### Measures

All measures are summarised in Table 2.

**Table 2 Tab2:** Screening and data collection across the trial

	Completed by	Baseline	End of Therapy	9 weeks	20 weeks	40 weeks	52 weeks
ASSESSMENTS							
Primary Outcomes							
WSAS	P	X		X	X	X	X
Secondary Outcomes							
PHQ-15	P	X		X	X	X	X
PHQ-9	P	X		X	X	X	X
GAD-7	P	X		X	X	X	X
PPS Questionnaire	P	X		X	X	X	X
CGI-patient	P	X		X	X	X	X
CSRI	P	X		X	X	X	X
EQ-5D-5 L	P	X		X	X	X	X
Process Variables							
Therapy Process Indicators							
*Treatment Attendance and Homework Log*^b^	T						
*Treatment Adherence*^b^	T						
*Treatment Fidelity*	IC		X				
*Competence Rating*	IC		X				
Satisfaction with Treatment^a^	P				X	X	X
CGI-therapist	T		X				
PSYCHLOPS^a^	P	X		X	X	X	X
Mechanisms of Change							
*CBRQ*	P	X		X	X	X	X
*Acceptance Scale*	P	X		X	X	X	X
Baseline							
Demographic Variables	P	X					
Clinical Information	P	X					
Preferred Treatment Group	P	X					
Therapist Background Measures	T	X					
Other							
Concomitant Medications	P	X		X	X	X	X
Serious/Adverse Events	P				X	X	X

*WSAS* work and social adjustment scale, *PPS Questionnaire* persistent physical symptoms questionnaire, *PHQ-9* patient health questionnaire – 9 item scale, *GAD-7* generalised anxiety disorder – 7 item scale, *PHQ-15* patient health questionnaire – 15 item scale, *CGI* clinical global impression scale, *CBRQ* cognitive behavioural responses questionnaire, *CSRI* client service receipt inventory, *EQ-5D-5 L* EuroQol 5 Dimension 5 Level, *PSYCHLOPS* psychological outcome profiles, *P* patient, *IC* independent clinician, *T* therapist. ^a^ Assessment only completed by participants assigned to the intervention group. ^b^ completed after each therapy session

#### Baseline

*Demographic Variables:* A number of baseline demographic variables will be collected in order to describe the sample. This includes gender, age, ethnicity, occupational status, educational attainment, living arrangements, native language, and the clinic that the patient was recruited from (i.e. cardiology, neurology, rheumatology, respiratory, gastroenterology, urology and other)**.***Clinical information****:*** Patients will be asked to provide clinical information on their symptoms. This includes;
◦ Current diagnosis◦ Duration of symptoms◦ Comorbid medical diagnoses◦ Concomitant medication◦ Fibromyalgia assessment: a 4-item measure which assesses whether the participant meets the criteria for fibromyalgia.◦ Health of relative/ close friend: a 4-item measure which assesses the medical history of family and close friends (i.e. heart condition, stroke, neurological condition, condition similar fibromyalgia).◦ The AUDIT alcohol consumption questions (AUDIT-C): a 3-item scale with a range of scores from 0 to 12 measuring alcohol consumption [22].
3.*Preferred treatment group****:*** Patients will be asked to indicate their treatment preference post randomisation (i.e. CBT plus SMC, SMC alone, or no preference).4.*Therapist Background Measures:* this will include gender, professional background, number of years of experience, full time/part tome status, number of PPS patients treated, highest education level.

#### Primary outcome measures

*Functional Impairment*: the Work and Social Adjustment Scale (WSAS) is a 5 item scale used to measure the extent to which people’s problems interfere with their ability to carry out normal activities, go to work, partake in private and social activities and impact on relationships [23]. It is a valid and reliable scale which was chosen as it is a routine outcome measure in Increasing Access to Psychological Therapies (IAPT). It has also been used in several other randomised controlled trials evaluating psychological interventions for IBS and CFS [20, 23, 24].

#### Secondary outcome measures

*Physical Symptoms****:*** the Patient Health Questionnaire 15 (PHQ15) will be used to measure somatic symptoms [25]. Each item is rated on a 3- point Likert scale (0 = not bothered at all; 1 = bothered a little; 2 = bothered a lot) and the total score can range from 0 to 30 where a higher score indicates higher symptom severity. The PHQ15 is a brief well-validated tool for detecting somatisation [26].*Depression:* the Patient Health Questionnaire-9 (PHQ-9) will be used to monitor and measure the severity of depression in participants [27]. Each item is rated on a 4-point Likert scale (0 = not at all; 1 = several days; 2 = more than half the days; 3 = nearly every day) and the total score can range from 0 to 27 where a higher score indicates greater depressive severity. The PHQ-9 is a reliable and well-validated measure of depression severity [26].*Anxiety****:*** the Generalised Anxiety Disorder – 7 (GAD − 7) questionnaire will be used to measure the severity of GAD in participants [28]. Each item is rated on a 4- point Likert scale (0 = not at all; 1 = several days; 2 = more than half the days; 3 = nearly every day) and the total score can range from 0 to 21 where a higher score indicates greater anxiety. The GAD-7 has demonstrated reliable psychometric properties in the measurement of anxiety in the general population[29].*The main presenting symptom:* The Persistent Physical Symptom Questionnaire is comprised of three scales to measure (i) severity, (ii) distress and the (iii) problematic nature of the patients main presenting symptom (e.g., chest pain). Each item is scored on a 10-point scale (from 1 = not at all to 10 = extremely). Average scores from the three scales will be used to calculate an overall interference score. This measure was adapted from the Chest Pain questionnaire, which has been previously used for patients with non-cardiac chest pain [30].*Global Outcome:* the adapted Clinical Global Impression (CGI patient) will be used to measure global change. It has been used in many previous trials of psychosocial treatments [31]. This is rated on a 9-point Likert scale where 1 is completely recovered and 9 is could not get any worse.*Costs (Client Service Receipt Inventory):* the self-report Client Service Receipt Inventory will be used to assess health service use, informal care, lost work time and financial benefits [32].*EuroQoL 5D:* the EQ-5D is a reliable and valid tool to measure health related quality of life [33]. Each dimension (mobility, self-care, usual activity, pain/discomfort and anxiety/depression) is rated on 5 levels (1 = no problems; 2 = slight problems; 3 = moderate problems; 4 = severe problems; 5 = extreme problems). The participant will also rate their own perception of their current health on a visual analogue scale ranging from 0 to 100 (0 = the best health you can imagine to 100 = the worst health you can imagine).

#### Process variables

*Therapy Process Indicators*
*Treatment attendance and homework log:* Therapist will be asked to report
i.Patient attendanceii.Reasons for session cancellation if cancellediii.Mode of delivery (face to face or by telephone)iv.Length of sessionv.Provision of handoutsvi.Percentage of homework completed as rated by the therapistvii.Number of unplanned telephone calls*Treatment adherence:* Treatment adherence will be rated by the CBT therapist at the end of treatment. The therapist will rate how well the participant adhered to treatment and to what extent they accepted the therapy model. This will be rated on a 4-point Likert scale.*Competence rating*: *a questionnaire completed by the fidelity raters assessing the therapist competence.**Satisfaction with treatment (CBT plus SMC only):* Satisfaction of treatment will be measured at week 20. Participants will be asked to rate how satisfied they were with the CBT treatment on a 7-point Likert scale (1 Very dissatisfied; 2 Moderately dissatisfied; 3 Slightly dissatisfied; 4 *Neither; 5 Slightly satisfied; 6 Moderately satisfied; 7 Very satisfied).**Global Improvement (therapists) (CBT plus SMC only):* At the end of treatment, CBT therapists will rate how much the participant changed since the start of the study using an adapted version of the Clinical Global Impression (CGI therapist). This will be rated on a 9-point Likert scale where is 1 is completely recovered and 9 is could not get any worse.*Self-Rated Patient-Defined Problem (CBT plus SMC only)*: Participants in the CBT plus SMC group only will be asked to complete the PSYCHLOPS questionnaire. The PSYCHLOPS is a well validated and reliable patient-generated measure [34], which assesses function and well-being on problems that are reported by the participant. As the problems are significant to the participant, it is highly sensitive to change and can be measured throughout the trial. Participants are asked to describe their main problem or problems and how it affects them. All responses to questions are scored.

*Mechanisms of Change: A separate analysis plan will be written for the mediation analysis.*
*The Cognitive Behavioural Responses Questionnaire (CBRQ*) is a valid and reliable tool used to assess participants cognitive and behavioural responses to their symptoms [35]. Each item is measured on a five-point Likert scale, scored from 0 (strongly disagree) to 4 (strongly agree) where a higher subscale score indicates more unhelpful cognitions and behaviours.*The Acceptance scale* is a 9-item subscale measuring pain willingness, taken from the Chronic Pain and Acceptance questionnaire [36] and adapted to focus on willingness to accept symptoms. Participants will be asked to rate each item as its applied to them on a 7-point Likert scale (0 = never true to 6 = always true); where a higher score will indicate greater acceptance.

### Data collection plan: retention

Retention rates will be monitored and potentially boosted by providing participants with options regarding completion of questionnaires. These will include via post, telephone or email. Thank-you cards will be sent mid trial and end of trial.

### Statistical analysis

A statistical analysis plan (SAP) will be developed by the statisticians and agreed with the trial team before database lock. The formal statistical analyses will estimate the difference in mean outcomes between patients randomised to CBT plus SMC and SMC by intention to treat at the various post-treatment observation time points. Estimates of effect sizes together with 95% confidence intervals will be reported. It is planned that the main statistical analysis will use a linear mixed model with maximum likelihood estimation. The data will be analysed on an intention to treat basis.

The linear mixed model will contain post-treatment measures of the primary outcome (at the four follow up time points, i.e. 9, 20, 40 and 52 weeks) as the dependent variables. Fixed effects will consist of:
Baseline measures of WSAS;Trial arm;Dummy variables for time points (9, 20, 40 or 52 weeks);Trial arm Χ time interaction terms;Dummy variables for treatment clinic (randomisation stratifier).Dummy variable for disability level (randomisation stratifier)Dummy variables for therapist

Baseline measures of the outcome variable are included as they are known predictors of the outcome and thus should help us to gain precision for effect estimates of interest.

A random effect for participant will be entered into the model to account for correlations between the four repeated measures per participant. A more complex correlation structure (e.g. random intercept and slope model) may be considered if it proved to provide a better model fit.

Standardised effect sizes will be computed to measure the effect of treatment on primary and secondary outcomes at various assessment time points. This will be done by dividing the estimated trial arm difference by the baseline standard deviation of the measure.

We will investigate empirically whether non-adherence with CBT predicts loss to follow-up, and if this were the case, we will use multiple imputation instead of linear mixed modelling to generate inferences that are valid under a realistic missing at random assumption.

We will ensure that patterns of missing data and reasons for missingness are consistent with the CONSORT diagram. Baseline characteristics will be assessed to see if they predict missingness, if so, they will be included in the analysis model. We will check if any post randomisation variables such as compliance are predictive of missingness, and if so this will inform our missing data approach.

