### Proposed sample size

The sample size is based on a previous study: a RCT of rehabilitative treatments for chronic fatigue syndrome [20]. We used data from this trial as it also used the work and social adjustment as an outcome. Based on the White et al. study, we calculated a treatment effect of − 3.6 points on WSAS comparing CBT at 12 months. The within-group SD at 12 months was estimated to be 9.4 points giving a standardised effect size of Cohen’s d = 3.2/9.4 = − 0.38. The sample size calculation (Stata command sampsi) suggests that 161 patients per arm (322 in total) are needed to detect this effect size or a larger one with 90.14% power allowing for a deflation for including baseline measures in the analysis model (factor 0.84 assuming a correlation between baseline and 9-month WSAS of 0.4) and an attrition rate of 25%.

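### Planned maximum likelihood estimation makes the 52-week WSAS standard error about 1% to 1.7% too small; REML would correct this at no real cost

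*Protocol article*

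**What the plan says.** The protocol article's Statistical analysis section names the estimator: "It is planned that the main statistical analysis will use a linear mixed model with maximum likelihood estimation". The dependent variable is WSAS at 9, 20, 40 and 52 weeks, with a random effect for participant. The fixed effects are baseline WSAS, arm, time, arm by time, clinic, disability level and therapist.

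The same section lets the list grow: "Baseline characteristics will be assessed to see if they predict missingness, if so, they will be included in the analysis model". It gives no limit on how many such terms may enter.

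On reporting it says "Estimates of effect sizes together with 95% confidence intervals will be reported", and on what is still to come, "A statistical analysis plan (SAP) will be developed by the statisticians and agreed with the trial team before database lock". It mentions neither REML nor a degrees-of-freedom method.

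**The concern.** ML estimates the variance around the fitted fixed effects as if those effects were known, so it makes no deduction for having estimated them. The variance components come out slightly low, and so does the standard error of the 52-week contrast. REML makes the deduction and relies on the same missing-at-random argument.

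The terms that matter most are those that vary between participants, because their cost is set against the number of participants and not the number of observations. The clinic list has seven categories, so this model spends a noticeable number of such terms, and the rule on predictors of missingness can add more.

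At stake are the width of the primary 95% confidence interval and how closely the test holds its 5% level.

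**Working it through.** **Inputs from the protocol article**
- Sample size: 322 in total, 161 per arm; attrition 25% (Proposed sample size).
- Target difference: "3.6 points on WSAS comparing CBT at 12 months". SD: "The within-group SD at 12 months was estimated to be 9.4 points". Baseline correlation 0.4, so the variance factor is 1 − 0.4² = 0.84.
- Two-sided 5% level, inferred from the 95% intervals.
- Clinics: seven categories (Setting; Baseline), hence six dummies. Therapists: three, in the CBT arm only, hence two columns beyond arm.

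**Input assumed:** the residual within-participant correlation, which the article does not give. Values of 0.4, 0.55, 0.6 and 0.8 were used.

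**The plan's own figure.** SD after adjustment = 9.4 × √0.84 = 8.615. After attrition, 161 × 0.75 = 120.75, or 121 per arm. Power = Φ(3.6 / (8.615 × √(2/121)) − 1.96) = Φ(1.290) = 90.15%; with 120.75 it is 90.09%. The stated 90.14% is reproduced. (The section also prints 3.2 in the effect-size ratio. 3.2/9.4 = 0.34, whereas 3.6/9.4 = 0.38, the stated value, so 3.6 is used here.)

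**Counting terms.** Participant-level: intercept 1 + baseline WSAS 1 + arm 1 + clinic 6 + disability 1 = 10, or 12 with therapist. Adding 3 time and 3 arm-by-time terms gives 16 to 18 in all.

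**Rough bound.** SE(ML)/SE(REML) ≈ √((N − p)/N), with p the participant-level terms. Implied type I error = 2 × (1 − Φ(1.96 × ratio)).

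| N | p | ratio | implied type I error |
|---|---|---|---|
| 322 | 10 | 0.9843 | 5.4% |
| 322 | 12 | 0.9812 | 5.5% |
| 242 | 10 | 0.9791 | 5.5% |
| 242 | 12 | 0.9749 | 5.6% |

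N = 242 treats everyone lost to attrition as contributing nothing, which overstates the loss because most of them supply earlier visits.

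**Simulation of the listed model.** Null trials, 322 participants, four visits, 25% monotone dropout, random intercept, both estimators fitted to the same data; 4,000 trials per row, Monte Carlo error about 0.35 percentage points.

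| Residual correlation | Therapist terms | SE, ML | SE, REML | ratio | type I, ML | type I, REML |
|---|---|---|---|---|---|---|
| 0.4 | no | 1.0802 | 1.0916 | 0.9895 | 5.25% | 4.98% |
| 0.4 | yes | 1.0796 | 1.0930 | 0.9877 | 4.90% | 4.63% |
| 0.6 | no | 1.0559 | 1.0690 | 0.9877 | 5.20% | 4.85% |
| 0.6 | yes | 1.0546 | 1.0701 | 0.9855 | 5.50% | 5.33% |
| 0.8 | no | 1.0247 | 1.0395 | 0.9857 | 5.30% | 4.95% |
| 0.8 | yes | 1.0240 | 1.0418 | 0.9830 | 5.73% | 5.25% |

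The ML standard error is 1.05% to 1.7% low. Converting the extreme ratios as above gives type I error of 5.25% (0.9895) to 5.4% (0.983).

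**Larger runs.** At residual correlation 0.55, two separate sets of 20,000 null trials (Monte Carlo error about 0.15 points) both gave a ratio of 0.986. Type I error for ML against REML was 5.17% against 4.84% in one set and about 5.5% against 5.1% in the other. The simple averages are (5.17 + 5.5)/2 = 5.3% and (4.84 + 5.1)/2 = 5.0%.

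**Added covariates (number assumed).** With 10 extra columns the ratio is 0.9755, a shortfall of about 2.5%. Type I error was 5.29% against 4.69% in one set and about 5.6% against 5.1% in the other. With 20 extra columns, in one set only, the ratio is 0.9643 and the rates are 6.0% against 5.1%.

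**Size in WSAS points.** At correlation 0.6 with therapist terms, the half-width changes by 1.96 × (1.0701 − 1.0546) = 0.03 points. Against 3.6 points that is 0.03/3.6, or about 0.8% of the target difference.

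**The case against.** The strongest reply is that this is a preference between two accepted estimators. ML is asymptotically valid and handles data missing at random as REML does. Nothing in the article contradicts it, and the sample size is unaffected. The wording is a plan, not a lock: the SAP is still to come, and estimator settings can be set there. The phrase may also simply name likelihood-based modelling as the alternative to multiple imputation, which the section discusses later. All of this stands, and it is why the point is minor. But the article names ML explicitly, so it is a stated choice that an SAP would naturally inherit, not a detail left open.

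A second reply is that the type I error excess is simulation noise. For a single set that is arguable: 5.17% is about one Monte Carlo error above 5%. It does not survive the evidence taken together. The standard-error ratio is below 1 in every scenario, its direction follows from theory, and the two large sets average 5.3% for ML against 5.0% for REML.

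Some stronger readings are tempting and not supported:
- That the error favours CBT. A standard error that is slightly too small makes significance more likely in either direction, including against CBT.
- That ML ignores the fixed effects. It fits them and omits only the degrees-of-freedom deduction.
- That type I error reaches 6%. This needs 20 added columns. The article gives no number, and only characteristics found to predict missingness would enter.
- That every secondary outcome is equally affected. The model is set out for the primary outcome, and the section does not say outright that the secondaries use it.

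**Conclusion.** The point holds as a minor improvement. With the listed terms, ML understates the 52-week standard error by about 1% to 1.7%, and two-sided type I error is about 5.3% to 5.5%. The result rests on the assumed residual correlations, a random-intercept structure, monotone dropout of 25% and a two-sided 5% level. The figure of about 2.5% for a model enlarged with predictors of missingness rests on an assumed 10 columns.

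A reader might infer that the primary analysis is invalid or that the trial's conclusion is at risk. Neither follows: the discrepancy is unlikely to alter the conclusion unless the result falls almost exactly on the significance boundary.

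**What to change.** In the Statistical analysis section, and in the SAP when it is agreed, state that the final estimate of the 52-week difference and its confidence interval come from REML. Keep ML only for likelihood-ratio comparisons of models with different fixed effects. A Satterthwaite or Kenward-Roger correction is optional at this sample size.

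The cost is one phrase and one software option, with no extra data and no change to the sample size. The confidence interval becomes about 1% to 1.7% wider with the listed terms, and somewhat more if predictors of missingness are added.

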### Therapists

Three trained CBT therapists (clinical behavioural therapist or clinical psychologists) will provide CBT sessions. All therapists will receive training prior to delivering the CBT intervention to participants and supervision will be provided throughout the therapy. In case of resignation/parenting leave of a therapist, we will recruit a replacement therapist as quickly as possible. If a CBT session is missed due to therapist planned annual leave, the therapist will attempt to fit in the missing sessions within the five-month treatment period, but no more than one session will take place in any 1 week.

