### Standard medical care

Patients in both trial arms will receive SMC. SMC is defined as the continuation of any follow-up consultations as planned with specialised medical staff, including investigations, discussion of the PPS diagnosis, and the prescribing of any medication if required.

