### Randomisation

Participants will be randomly allocated to one of two trial arms, using a web-based randomisation system managed by the King’s Clinical Trials Unit (KCTU). Randomisation will be at the level of the individual, using block randomisation with random block sizes, stratified by clinic (e.g., cardiology, neurology etc.) and disability level (moderately severe impairment or significant impairment) as indicated by the Work and Social Adjustment Scale.

Treatment allocation will be communicated by email to the trial manager within a period of 24 h. The trial manager will inform the participant of their treatment group by telephone/email that same day. Following allocation to the treatment group the trial manager will inform the therapist, who will contact the participant to arrange the first session.

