## Discussion

PPS are highly prevalent in both primary and secondary care, and are associated with severe physical disability, psychological distress and high health care costs [3, 4, 6]. This paper outlines the study protocol of an RCT designed to evaluate the efficacy and cost-effectiveness of a transdiagnostic cognitive behavioural intervention for adults with PPS in secondary care. The PRINCE Secondary study will be the first trial worldwide to address the efficacy and cost-effectiveness of a manual-based, transdiagnostic, approach for PPS. If it proves to be efficacious, this treatment approach could significantly improve overall functioning in patients with PPS and may lead to substantial long-term economic benefits to the NHS. Moreover, this approach could also be potentially beneficial for treating patients with other debilitating long-term conditions, including diabetes, hypertension and chronic kidney disease.

There are several limitations that need to be considered when assessing the potential impact and implications of our findings. First, we do not have an attention control so any change that occurs in the transdiagnostic CBT group cannot be attributed to the specific contents of the intervention. Second, the present trial protocol deviates from the original protocol. The intention of this study was to recruit a representative sample of therapists to deliver the intervention. However, only three therapists were recruited as opposed to eight which was outlined in the original protocol. This protocol deviation led to the trial becoming an evaluation of the efficacy of CBT delivered by these three therapists. This change in trial objective also led us to recalculate the sample size requirement with the approval of Camberwell St Giles REC.

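### Therapist dummy variables sit beside the trial-arm term although only CBT patients have a therapist, so the listed terms do not by themselves define the arm-average effect

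*Protocol article*

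**What the plan says.** The Statistical analysis section of the Protocol article enumerates the fixed effects of the primary linear mixed model. Among them are trial arm, "Trial arm Χ time interaction terms" and "Dummy variables for therapist". It gives no value of the therapist variable for SMC patients, no reference category, no centring and no averaging over therapists.

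Three other sections show who has a therapist:

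- Therapists: "Three trained CBT therapists (clinical behavioural therapist or clinical psychologists) will provide CBT sessions".
- Randomisation: "Following allocation to the treatment group the trial manager will inform the therapist, who will contact the participant to arrange the first session".
- Standard medical care: "SMC is defined as the continuation of any follow-up consultations as planned with specialised medical staff".

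The target is stated separately. The analyses are to "estimate the difference in mean outcomes between patients randomised to CBT plus SMC and SMC by intention to treat", and Primary objectives sets the comparison at 52 weeks. The Discussion adds, on having three therapists instead of eight: "This protocol deviation led to the trial becoming an evaluation of the efficacy of CBT delivered by these three therapists". Standardised effect sizes are obtained by "dividing the estimated trial arm difference by the baseline standard deviation of the measure".

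**The concern.** Therapist is nested in the CBT arm: it is fixed after allocation and does not exist for SMC patients. Ordinary dummy variables for such a factor compete with the arm term for the same information. Software will either report a singularity and drop a column, or the analyst will choose a reference therapist. The coefficient labelled trial arm then no longer means CBT arm versus SMC arm.

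At stake are the meaning of the primary estimate, its dependence on an unstated coding choice that could be made after the data are seen, and its precision. The standardised effect sizes inherit the same problem, because the arm difference is their numerator.

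**Working it through.** **Inputs from Proposed sample size.** Effect -3.6 points, SD 9.4, 161 per arm, variance factor 0.84 (1 - 0.4²), attrition 25%, stated power 90.14%. Alpha is not given there. I assume 0.05 two-sided, in line with the 95% intervals in Statistical analysis.

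**Inputs not in the document (assumed).** Therapist caseloads, therapist-specific effects, and the intraclass correlation ρ of a patient's repeated WSAS scores after baseline adjustment.

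**1. The plan's own power.** Completers per arm: 161 × 0.75 = 120.75, taken as 121. Adjusted variance: σ² = 9.4² × 0.84 = 74.22. SE = √(2 × 74.22 / 121) = 1.108. Power = Φ(3.6/1.108 - 1.96) = 90.15%, against the stated 90.14%. The figure is reproduced, and it is the power of the arm-average comparison.

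**2. Rank.** Let A be the arm indicator and T1, T2, T3 the therapist dummies, all 0 for SMC. Then A = T1 + T2 + T3. The columns are intercept, arm, three time dummies, three arm-by-time terms and three therapist dummies: 11 columns, rank 10. A four-level therapist factor with SMC as its reference is the same case.

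**3. Meaning after one dummy is dropped.** There are now 10 columns, rank 10. The arm coefficient is identified, but it refers to the reference therapist's patients. Take illustrative therapist effects of -5.6, -3.6 and -1.6 versus SMC, constant over time, with 54, 54 and 53 patients:

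| Coding | Arm coefficient |
|---|---|
| Reference therapist 1 | -5.6 |
| Reference therapist 2 | -3.6 |
| Reference therapist 3 | -1.6 |
| No therapist term | -3.61 |
| Caseload-centred within CBT | -3.61 |

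With caseloads of 80, 50 and 31 the last two rows become -4.21 and the first three do not change. The list contains no therapist-by-time terms, so the reference therapist's offset is the same at every visit and passes unchanged into the 52-week contrast.

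**4. Precision.** Let n be the completers per arm, each seen at all four visits, and s the reference therapist's share of the CBT arm. Under a random-intercept model the reference-coded 52-week contrast is the arm-average contrast plus the reference therapist's deviation from the caseload average. That deviation is estimated from four-visit patient means, so

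Var = (σ²/n) × [2 + (1/s - 1)(ρ + (1 - ρ)/4)].

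The arm-average contrast has Var = 2σ²/n. With s = 1/3 and n = 121:

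| ρ | Variance ratio | SE | Power for -3.6 |
|---|---|---|---|
| 0.4 | 3.1/2 = 1.55 | 1.379 | 74% |
| 0.6 | 3.4/2 = 1.70 | 1.444 | 70% |
| 0.8 | 3.7/2 = 1.85 | 1.507 | 67% |
| 1 | 4.0/2 = 2.00 | 1.566 | 63% |

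The last row also equals a single-visit comparison of one third of the CBT arm with all of SMC. If the reference therapist treats 20% of CBT patients (s = 0.2), the ratio is 2.1 at ρ = 0.4 and 3.0 at ρ = 1, and power is 61% and 47%.

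**5. After repair.** A generalised-least-squares calculation on the same inputs gives SE 1.108 and power 90.15% with no therapist term, with caseload-centred contrasts, and with a caseload-weighted average taken after reference coding. All three agree with step 1.

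**The case against.** The strongest reply is that the section lists terms, not a parametrisation. Every coding of arm and therapist spans the same model space, and the caseload-averaged difference is estimable from it. Because arm-by-time terms are present, the 52-week result has to be built as a contrast after estimation anyway, and the stated target tells the analyst which contrast to build. This stands. A reader might infer that the plan will inevitably report one therapist's effect, or that the planned 90% power is already lost. The document supports neither: it does not say that a raw reference-coded coefficient is the reported effect, and step 5 shows no loss when the effect is averaged.

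Calling the reference-coded 52-week contrast one therapist's effect would also be imprecise. It carries that therapist's time-constant offset, while the arm-by-time part draws on all CBT patients.

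A second reply is that coding belongs to the statistical analysis plan, which is not shown. That holds for fine detail. But the article itself fixes the terms of the primary model, and followed literally they need a constraint that it does not give. An analysis plan that copies the list would inherit the problem.

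A third reply is that fixed therapist effects suit an evaluation of three named therapists. I agree. The fault lies in uncoded dummies beside the arm term, not in fixed effects.

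**Conclusion.** The point holds as a defect in how the primary model is specified. The rank deficiency, and the dependence of a reference-coded arm coefficient on the choice of reference, follow from the design and need no assumed numbers. Neither literal reading yields the arm-average intention-to-treat difference that the article sets as its target.

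The cost in precision is conditional. It arises only if the reference-coded contrast is reported as the treatment effect. Power for -3.6 would then be roughly 63-74% instead of about 90%, assuming equal caseloads, 121 completers per arm, SD 9.4, factor 0.84, two-sided alpha 0.05 and intraclass correlation 0.4 to 1. It would be lower if the reference therapist has a smaller caseload. The document gives neither the correlation nor the caseloads, and the therapist effects in step 3 are illustrations, not expectations.

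**What to change.** Either remove therapist from the primary model, or keep it as caseload-centred contrasts within the CBT arm, with the value 0 for all SMC patients. In both cases state that the primary 52-week effect is the caseload-weighted average over the three therapists, and that the standardised effect sizes use that same difference. Report between-therapist differences separately, as description.

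This keeps the inference to these three therapists and the planned power. It costs one line in the protocol and in the statistical analysis plan, needs no new data, and should be settled before the data are analysed by arm.
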